#### Statistical description and analysis methods

For continuous variables, normality will be assessed using the Shapiro-Wilk test or Kolmogorov-Smirnov test. If normally distributed, data will be presented as mean ± standard deviation, and between-group comparisons will be performed using independent sample t-tests. If not normally distributed, data will be presented as median and interquartile range (IQR), and the Mann-Whitney U test will be applied for between-group comparisons.

For categorical variables, descriptive statistics will be presented as frequencies and percentages. Between-group comparisons will be performed using the chi-squared test or Fisher’s exact test when the expected frequency in any cell is less than 5.

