#### Secondary outcomes

(1) Objective Response Rate (ORR): ORR represents the percentage of patients achieving a predefined reduction in tumor volume and maintaining this reduction for a specified minimum duration, assessed in accordance with RECIST 1.1 criteria.(2) OS: OS is the interval from randomization to death caused by any factor.(3) Quality of Life Assessment: The European Organization for Research and Treatment of Cancer Quality of Life Questionnaire-Core 30 (European Organisation for Research and Treatment of Cancer, 2001) and the Anderson Symptom Assessment Scale (Giesinger et al., 2021) will be employed to assess score changes.

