#### Allocation concealment

Complete allocation concealment will be maintained through the centralized web-based system, which will only reveal treatment allocation after confirming patient eligibility and completing all required baseline assessments. The randomization sequence will be generated and stored securely by the independent statistical unit, ensuring that investigators and research personnel remain blinded to upcoming assignments throughout the enrollment process.

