#### Time-to-event analysis

Kaplan-Meier curves will be used to estimate survival functions for overall survival (OS) and progression-free survival (PFS). The log-rank test will be employed to compare survival curves between treatment groups. Cox proportional-hazards models will be applied to calculate hazard ratios (HRs) with corresponding 95% confidence intervals (CIs), adjusting for pre-specified prognostic factors including ECOG performance status, number of prior treatment lines, and presence of liver metastases. Patients will be censored at the date of last contact for survival analyses and at the date of last tumor assessment for progression-free survival analyses.

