#### Primary and secondary analyses

The primary efficacy analysis will be conducted on the mITT population, with supportive analyses performed on the PP population. Safety evaluations will utilize the safety set. The primary endpoint analysis will focus on PFS, while secondary endpoints will include response rate, OS, quality of life measures, and safety parameters.

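### Quality-of-life and symptom score changes are compared by a test that a normality pre-test selects, without the baseline score as a covariate: valid, but less precise than it could be and with no fixed effect measure

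*Protocol article*

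**What the plan says.** All references are to the protocol article.

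- **Secondary outcomes:** the EORTC QLQ-C30 and the Anderson symptom scale "will be employed to assess score changes".
- **Primary and secondary analyses:** "secondary endpoints will include response rate, OS, quality of life measures, and safety parameters".
- **Statistical description and analysis methods:** "For continuous variables, normality will be assessed using the Shapiro-Wilk test or Kolmogorov-Smirnov test". If normality holds, "between-group comparisons will be performed using independent sample t-tests", with mean and SD reported. If not, "the Mann-Whitney U test will be applied for between-group comparisons", with median and IQR reported. The section does not say which of the two normality tests decides.
- **Time-to-event analysis:** the only covariate adjustment in the article is in the Cox models, "adjusting for pre-specified prognostic factors including ECOG performance status, number of prior treatment lines, and presence of liver metastases". None is stated for a continuous outcome.
- **Allocation concealment:** the assignment is released only after confirming eligibility and "completing all required baseline assessments". Quality of life is not named there, but a change score cannot be formed without a baseline score.

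**The concern.** A change score fixes the weight of the baseline value at 1. A model with baseline as covariate estimates that weight from the data. When baseline and follow-up are imperfectly correlated, the fixed weight is too large: the change score over-corrects for chance imbalance at baseline and adds noise. With 30 patients per arm, and fewer at later visits, that noise widens the intervals noticeably.

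The pre-test raises a second issue. The t-test goes with a difference in means and Mann-Whitney with a rank comparison. If a normality test on about 30 values per arm chooses between them, the quantity reported can differ from scale to scale and visit to visit for reasons unrelated to the question asked. Results on the different quality-of-life scales could then not be set side by side.

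**Working it through.** The article gives no SD, effect size, power or baseline to follow-up correlation for quality of life, so there is no stated figure to reproduce.

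**Inputs.** From the article: 30 per arm, 1:1 allocation, two-sided alpha 0.05. Assumed: equal SD s at baseline and follow-up, complete data, and correlation rho of 0.3, 0.5 or 0.7.

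**Step 1, variance per patient.**

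- Change score: 2(1−rho)s².
- Baseline-adjusted: (1−rho²)s².
- Ratio, adjusted to change: (1−rho²)/[2(1−rho)] = (1+rho)/2, which is below 1 for every rho below 1.

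**Step 2, 95% CI half-width in units of s.** Change score: t(58 df) × √(2 × variance/30). Adjusted: the same with 57 df and the variance multiplied by 1 + 1/56, an approximate penalty for one covariate.

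| rho | Change variance | Adjusted variance | Ratio | 60/ratio | Half-width, change | Half-width, adjusted |
|---|---|---|---|---|---|---|
| 0.3 | 1.40 | 0.91 | 0.65 | 92 | 0.61 | 0.50 |
| 0.5 | 1.00 | 0.75 | 0.75 | 80 | 0.52 | 0.45 |
| 0.7 | 0.60 | 0.51 | 0.85 | 71 | 0.40 | 0.37 |

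The column 60/ratio is the total number of patients that the unadjusted change comparison would need to match the adjusted analysis of 60, before the covariate penalty. With the penalty the ratios become 0.66, 0.76 and 0.87.

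**Step 3, the rule as planned, including the pre-test.** Simulation with 4,000 trials per scenario and 30 per arm. Follow-up = rho × baseline + √(1−rho²) × error, plus 0.5 SD in one arm where an effect is present. Shapiro-Wilk is applied to the changes in each arm at 5%, and Mann-Whitney is used if either arm fails. The comparator is a linear model with arm and baseline only.

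| Errors | rho | Power, planned rule | Power, baseline-adjusted |
|---|---|---|---|
| Normal | 0.3 | 36% | 51% |
| Normal | 0.5 | 47% | 58% |
| Normal | 0.7 | 68% | 75% |
| Exponential | 0.3 | 41% | 54% |
| Exponential | 0.5 | 57% | 61% |
| Exponential | 0.7 | 83% | 76% |

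**Step 4, what the gate does.** With normal errors about 10% of trials still go to Mann-Whitney, as expected from two tests at 5%: 1 − 0.95² = 0.0975. With exponential errors 60% to 89% do. Type I error of the planned rule was 4.8% to 5.7% over the six null scenarios; the simulation standard error is √(0.05 × 0.95/4,000) = 0.3 percentage points.

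**The case against.** The strongest objection is that the link to quality of life is inferred. The methods section speaks of continuous variables in general and names neither instrument, and a condensed article may leave a quality-of-life model to an analysis plan that is not shown. This stands in part: the absence of a baseline covariate is read from silence. But the rule is stated for all continuous variables, the article gives no other for these scores, and where the article does intend adjustment, in the Cox models, it says so. A different model in the analysis plan would depart from the published rule.

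Several stronger readings are tempting, and the article does not support them:

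- **That baseline is ignored.** It is not; a change score subtracts it. What is missing is baseline as a covariate.
- **That the comparison is biased or inflates false positives.** Under randomisation the change-score comparison is unbiased, and the simulated type I error stayed near 5%.
- **That adjustment always wins.** With exponential errors and rho 0.7 the planned rule had 83% power against 76%. The (1+rho)/2 ratio describes the t-test branch only.
- **That phase III will be sized on a quality-of-life effect.** The Sample size section ties the pilot to median PFS and variance, and the limitations in the Discussion speak of effect-size data only in general. No quality-of-life effect or SD is named for that purpose.

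It is also fair to say that in refractory stage IV disease many follow-up scores will be lost to progression and death. The equivalent-patient figures assume complete data, and baseline adjustment does not repair that loss or the use of last observation carried forward.

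**Conclusion.** The point holds as one of efficiency and consistent reporting. For roughly normal scores with equal SDs and complete data, the planned comparison gives up 35%, 25% or 15% of the variance at assumed rho of 0.3, 0.5 or 0.7. At rho 0.7 this is modest: the half-width falls only from 0.40 to 0.37 SD. With strong skew and high rho the power advantage can go the other way, although the rank test then supplies no mean difference to report.

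The switching effect measure does not depend on rho. It follows from the gate itself and arises in about one comparison in ten even when the data are normal.

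The importance is minor to moderate. Quality of life is a secondary endpoint, the article declares no power for efficacy, and the log-rank and Cox analyses of PFS are untouched.

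**What to change.** For each continuous quality-of-life or symptom score, prespecify a linear model, or its repeated-measures form over the visits, with arm, baseline score and the minimisation factors (tumour location, ECOG group, centre). The endpoint can remain the change: once baseline is a covariate, the arm effect is the same whether change or follow-up score is the outcome. Report the adjusted mean difference with its 95% CI for every scale, with robust or bootstrap intervals if residuals are skewed. Drop the normality gate and keep a rank-based test as a sensitivity analysis only, which covers the skewed case in which it may be the more powerful test.

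The change is to wording only, with no extra patients, visits or data. The statistical cost is a few degrees of freedom. The figures above are for baseline alone. The minimisation factors add 1 + 1 + 4 = 6 terms with five centres. Extending the penalty used above to seven covariates gives roughly 1 + 7/50 = 1.14 if the six added factors predict nothing and are left to simple randomisation, so the ratios would be at worst about 0.74, 0.86 and 0.97. Minimisation keeps these factors close to balance, so the real cost should be smaller. If follow-up numbers become small, a simpler handling of centre should be fixed in advance.

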### Randomization, allocation concealment and blinding

#### Randomization strategy

Participants will be randomly assigned to the control or experimental group in a 1:1 ratio using minimization randomization. Given our sample size of 60 patients, we implemented minimization rather than traditional stratified block randomization to ensure balanced allocation across multiple prognostic factors without creating formal strata that might have insufficient sample sizes. The minimization algorithm will consider three key factors: (1) primary tumor location (colon vs. rectal cancer), (2) ECOG performance status (0-1 vs. 2), and (3) study center. This approach is particularly suitable for smaller trials as it ensures balanced allocation across multiple factors while maintaining statistical efficiency.

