#### Sample size

Many patients experience rapid disease progression with third- and fourth-line therapies, leaving them with limited therapeutic options. BJOEI has shown potential benefits for these patients.As an external pilot RCT, this study is not powered to test efficacy. A total of 60 participants (30 per arm) was selected to provide adequate precision for estimates of median PFS and variance while remaining logistically feasible. This aligns with published recommendations (15–25 per arm) and will inform the definitive phase III sample-size calculation (Sim and Lewis, 2012; Whitehead et al., 2016).

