### Statistical significance

All statistical tests will be two-sided, with a significance level of α = 0.05.

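### Response and adverse events are compared between arms only by a chi-squared or Fisher test at 0.05; a pilot meant to supply effect sizes for phase III should give risk differences with 95% confidence intervals

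*Protocol article*

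**What the plan says.** All references are to the protocol article.

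- **Statistical description and analysis methods** sets one rule for all categorical data. On description: "For categorical variables, descriptive statistics will be presented as frequencies and percentages". On comparison: a chi-squared test, or Fisher's "exact test when the expected frequency in any cell is less than 5". Adverse events and response are not named there, but both are categorical and no other method is given for them.
- **Statistical significance** has no exemption: "All statistical tests will be two-sided, with a significance level of α = 0.05".
- **Primary and secondary analyses** gives the status of these outcomes: "secondary endpoints will include response rate, OS, quality of life measures, and safety parameters".
- **Time-to-event analysis** is the only place that names an effect estimate with an interval: "Cox proportional-hazards models will be applied to calculate hazard ratios (HRs) with corresponding 95% confidence intervals (CIs").
- **Sample size** says: "As an external pilot RCT, this study is not powered to test efficacy". It justifies the number by precision: "A total of 60 participants (30 per arm) was selected to provide adequate precision for estimates of median PFS and variance".
- **Study objectives** and **Discussion** describe the purpose as preliminary data for a phase III trial of efficacy and safety, with effect-size data for its sample size and findings that generate hypotheses.

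**The concern.** The article chose estimation for the survival outcomes and testing for the proportions. For a trial whose product is parameters for a later trial, a p-value on response or on an adverse event is the less useful output. It gives neither the size of the difference nor the range of differences still compatible with the data.

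The weakness matters most for safety. Most individual adverse events in 60 patients will be sparse, and there the stated test rarely reaches 0.05 even when the risk differs materially. With an unrestricted 0.05 level, the natural summary line for each event is significant or not significant, and neither answers what phase III planners need to know: how large an excess cannot yet be excluded.

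**Working it through.** **Inputs.** From the article: 30 patients per arm (Sample size); two-sided 0.05 (Statistical significance); Fisher if any expected count is below 5, otherwise chi-squared, taken here without continuity correction (Statistical description and analysis methods). The true event risks below are assumptions, because the article gives none. There is no plan figure to reproduce: no power, event rate or precision target is stated for any proportion.

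**1. When Fisher applies.** With equal arms, the smallest expected count for an event seen in *k* of 60 patients is *k*/2 (for *k* up to 30). It is below 5 when *k* < 10, so any event seen in nine patients or fewer goes to Fisher.

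**2. One table, 5/30 versus 0/30.** The smallest expected count is 5/2 = 2.5, so Fisher is used.

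p = 2 × C(30,5)/C(60,5) = 2 × 142,506/5,461,512 = 0.0522, not significant.

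Neighbouring tables:

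| Events | Fisher p |
|---|---|
| 4 v 0 | 0.112 |
| 5 v 0 | 0.052 |
| 6 v 0 | 0.024 |
| 7 v 1 | 0.052 |
| 8 v 1 | 0.026 |

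**3. The same table as an estimate.** The difference is 5/30 − 0/30 = 0.167. The Wilson 95% limits are 0.073 to 0.336 for 5/30, and 0 to 0.114 for 0/30. The Newcombe limits are:

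- lower: 0.167 − √[(0.167 − 0.073)² + (0.114 − 0)²] = 0.020
- upper: 0.167 + √[(0.336 − 0.167)² + (0 − 0)²] = 0.336

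So the excess is 16.7 points, 95% CI 2.0 to 33.6. The score method gives 4.4 to 33.7.

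**4. No events in one arm.** The exact upper 95% limit for 0/30 is 1 − 0.025^(1/30) = 0.116, so a true risk of up to 11.6% remains possible.

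**5. How often the rule reaches p < 0.05.** For each pair of true risks, the binomial probabilities of all 31 × 31 tables with p < 0.05 under the article's rule were added. The last column does the same for a Newcombe 95% interval that excludes zero.

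| True risks (assumed) | Article's rule | Newcombe excludes 0 |
|---|---|---|
| 15% v 5% | 10.5% | 17.3% |
| 20% v 5% | 27.5% | 36.4% |
| 30% v 10% | 46.8% | 48.7% |
| 50% v 20% | 69.2% | 69.2% |
| 4.7% v 0% | 0.2% | 1.2% |

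The last row uses the response rate that the Introduction quotes for fruquintinib monotherapy, set against an assumed zero.

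**6. Actual error rate of the rule when the arms do not differ.** 0.15% at a common risk of 5%, 1.2% at 10%, 4.2% at 20%, 4.9% at 30% and 5.2% at 50%. The test is very conservative for sparse events and close to nominal for common ones.

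**The case against.** The case on the other side is substantial, and much of it stands.

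- **The counts will be visible.** Frequencies and percentages are reported, so 5 versus 0 would appear as 16.7% versus 0%. This stands: the excess is not hidden, only its uncertainty is left unquantified.
- **No rule equates non-significance with safety.** A reader might infer that the pilot will report no difference in harm and carry that into phase III. The article does not say so; it calls the trial unpowered and its findings hypothesis-generating. That reading is not supported.
- **The sample size, more than the test, limits detection.** A reader might blame Fisher's test for the insensitivity. Step 5 shows otherwise: using the interval as a detector raises 10.5% only to 17.3%, and leaves response at 4.7% versus 0% almost undetectable. This stands. The gain from an interval lies in what it reports, with little gain in power.
- **5 versus 0 is a borderline table.** With 5/29 versus 0/30, p = 0.024. Minimization and the safety set do not guarantee 30 in each arm. This stands, so the table serves only as an illustration. At 4 versus 0 the Newcombe interval (−0.6 to 29.7 points) also includes zero.
- **Intervals for proportions are often left to the analysis plan, which is not shown.** True, and their absence alone would be no finding. What remains is what the article does fix: testing as the between-arm comparison for proportions, and a 0.05 level that covers every test. Intervals added in an analysis plan would not by themselves lift that level from the safety comparisons.

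**Conclusion.** The point holds as a mismatch between the stated method and the trial's purpose. The only between-arm comparison stated for response and adverse events is a two-sided 0.05 test. At 30 per arm that test flags 15% versus 5% about 11% of the time and 20% versus 5% about 27%, mainly because of the sample size and partly because Fisher's test is conservative below about 20% risk. A p-value alone does not show how large an excess remains possible, which is the quantity phase III needs.

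The percentages rest on assumed true risks, exactly 30 evaluable patients per arm and an uncorrected chi-squared test. The chi-squared/Fisher rule is a standard convention and is correctly stated. The primary PFS analysis is unaffected, and no result would be invalidated. This is a worthwhile improvement to secondary and safety reporting at almost no cost.

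**What to change.** In *Statistical description and analysis methods*, state that for objective response and adverse events the main between-arm summary is the per-arm proportion with an exact 95% CI and the risk difference with a 95% CI (Newcombe or Miettinen-Nurminen).

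In *Statistical significance*, state that the 0.05 level does not apply to safety comparisons and that a non-significant result is not evidence of no harm.

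The cost is one sentence in each place, using standard software output and no extra data. The price is in the reporting: the report can no longer rest on an absence of significant differences in adverse events, and the intervals will be wide, as they should be with 30 patients per arm.

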#### Time-to-event analysis

Kaplan-Meier curves will be used to estimate survival functions for overall survival (OS) and progression-free survival (PFS). The log-rank test will be employed to compare survival curves between treatment groups. Cox proportional-hazards models will be applied to calculate hazard ratios (HRs) with corresponding 95% confidence intervals (CIs), adjusting for pre-specified prognostic factors including ECOG performance status, number of prior treatment lines, and presence of liver metastases. Patients will be censored at the date of last contact for survival analyses and at the date of last tumor assessment for progression-free survival analyses.

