#### Technical implementation

The randomization process will be overseen by an independent third-party statistical unit, specifically Beijing InnoTech Science & Technology Co., Ltd. A centralized web-based randomization system will implement the minimization algorithm using a computer-generated sequence with a random component (80% deterministic allocation based on minimization, 20% random allocation) to maintain unpredictability while achieving optimal balance. This ratio was selected to optimize both treatment balance and allocation concealment according to established recommendations for minimization algorithms in clinical trials.

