However, the study design has several limitations. Firstly, obtaining a placebo for BJOEI in China is challenging, making it impossible to blind the study. Secondly, this study is a small-scale trial intended to provide effect size data for calculating sample sizes in future large-scale randomized controlled trials. Thirdly, since the experiment will be conducted in five centers within China, we now clearly state that the findings may primarily reflect outcomes in the Chinese population and that caution should be exercised when extrapolating results to other ethnic groups due to potential pharmacogenomic differences.

The present findings will be hypothesis-generating and will supply the parameters necessary for a rigorously powered confirmatory phase III trial. We anticipate that this trial will offer a new treatment option for advanced CRC patients who are unresponsive to standard therapies.

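### Allocation is minimised on tumour location, ECOG and centre, but the PFS analysis names only ECOG of the three and does not say whether the log-rank test or the Cox model is primary (minor)

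*Protocol article*

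**What the plan says.** All places are in the Protocol article.

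- **Randomization strategy:** "Participants will be randomly assigned to the control or experimental group in a 1:1 ratio using minimization randomization". The three factors, which the section presents as prognostic, are listed as "1) primary tumor location (colon vs. rectal cancer), (2) ECOG performance status (0-1 vs. 2), and (3) study center".
- **Technical implementation:** the random element is "80% deterministic allocation based on minimization, 20% random allocation".
- **Time-to-event analysis:** "The log-rank test will be employed to compare survival curves between treatment groups", with no strata named. Hazard ratios come from Cox models "adjusting for pre-specified prognostic factors including ECOG performance status, number of prior treatment lines, and presence of liver metastases".
- **Primary and secondary analyses:** PFS in the mITT population is primary. The section does not say whether the log-rank test or the adjusted Cox model decides.
- **Statistical significance:** every test is two-sided at 0.05.
- **Sample size:** "As an external pilot RCT, this study is not powered to test efficacy", and "A total of 60 participants (30 per arm) was selected to provide adequate precision for estimates of median PFS and variance".
- **Discussion:** "the experiment will be conducted in five centers within China". The results are to be hypothesis-generating and to supply effect-size data for phase III.

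**The concern.** An analysis normally reflects the factors used to balance the allocation. Balancing on prognostic factors makes the arms more alike than chance would. A test that ignores those factors still carries their variation in its standard error, so it can be conservative and waste information. Here the log-rank names none of the three factors, and the Cox list omits tumour location and centre.

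The second part is the missing ranking. An unadjusted p-value and an adjusted hazard ratio come from different models and can disagree, and nothing says which one counts. A hazard ratio also depends on the covariates in the model, so the effect handed to the phase III design depends on a choice left open.

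What is at stake is the efficiency and clarity of the PFS effect estimate. No power target is at stake, because none is stated.

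**Working it through.** **Is there a figure of the plan to reproduce?** Only 2 × 30 = 60. No median, hazard ratio, event number or power is given, so 60 cannot be derived further. For context, Schoenfeld's approximation with 54 events (about the number in the simulations at HR 0.5) gives √54/2 × ln 2 − 1.96 = 2.55 − 1.96 = 0.59, that is 72% power at HR 0.5. The corresponding power at HR 0.6 is 47%.

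**Factors side by side.**

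| Factor | Minimisation | Log-rank | Cox list |
|---|---|---|---|
| ECOG | yes (0-1 vs 2) | not named | named |
| Tumour location | yes (colon vs rectal) | not named | not named |
| Centre | yes (five) | not named | not named |
| Prior lines | no | not named | named |
| Liver metastases | no | not named | named |

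**Simulation inputs from the article:** n = 60, 1:1, the three factors, five centres, 12 months of follow-up, two-sided 0.05. The 80/20 rule can be read in two ways, and both were run. If the random part is a 1:1 draw, the favoured arm has probability 0.80 + 0.20 × 0.5 = 0.90. Read as a biased coin, it has 0.80.

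**Assumptions not in the article:** exponential PFS with a 2-month median, about 2% censoring a month, 40% rectal, 30% ECOG 2, equal centres. Three prognostic strengths were used:
- none;
- moderate: location HR 1.3, ECOG HR 1.8, centre SD 0.2 on the log-hazard scale;
- strong: location HR 1.5, ECOG HR 2.5, centre SD 0.4.

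Prior lines and liver metastases were not simulated.

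**Results** (10,000 trials per scenario, favoured-arm probability 0.90, %; power at HR 0.5):

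| Strength | Size: log-rank | Size: Cox, ECOG | Size: Cox, ECOG + location | Power: log-rank | Power: Cox, ECOG | Power: Cox, ECOG + location |
|---|---|---|---|---|---|---|
| None | 5.5 | 5.8 | 5.9 | 68.8 | 68.5 | 68.7 |
| Moderate | 5.0 | 5.4 | 5.7 | 65.0 | 68.1 | 69.1 |
| Strong | 3.6 | 4.2 | 4.7 | 55.8 | 61.2 | 63.6 |

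Monte Carlo standard error is about 0.2 points for size and 0.5 for power. With probability 0.80 the log-rank size is 5.3, 5.1 and 3.8%. A separate run of 4,000 trials gave 5.0% (moderate) and 4.1% (strong).

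**Splitting the power gap.**
- Moderate: 69.1 − 65.0 = 4.1 points, of which ECOG gives 68.1 − 65.0 = 3.1 and location 1.0.
- Strong: 63.6 − 55.8 = 7.8 points, of which ECOG gives 61.2 − 55.8 = 5.4 and location 2.4.

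The tests differ in size (5.0 against 5.7%, and 3.6 against 4.7%), so part of each gap is not real efficiency.

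**Does minimisation raise false positives?** No. Under simple 1:1 randomisation the log-rank size was 5.6, 5.6 and 5.4%, no lower than under minimisation.

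**Can all three factors simply be added?**
- Four centre indicators in the Cox model: size 7.3% (moderate) and 6.9% (strong). A smaller run of 1,500 trials gave 8.5%. The inflation is also there under simple randomisation (7.2 and 7.0%), so it comes from too many parameters for the events, not from minimisation.
- Cox model stratified by centre: size about 6.5-6.6%, with no power gain over ECOG and location in the 4,000-trial run.
- Log-rank stratified on all three factors (2 × 2 × 5 = 20 strata): size 4.9 and 5.5%, but power only 45.0 and 44.1%.
- Log-rank stratified on location and ECOG only: power 63.7 and 58.6%, below the Cox model with the same two factors.

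**The case against.** The strongest reply has four parts.

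1. **The list is open and the article is condensed.** The Cox covariates are introduced as examples, and strata and centre handling are often left to an SAP. This stands in part: the article does not say that location is excluded or that the log-rank will be unstratified. But it does present a pre-specified list, and that list names two factors outside the minimisation while leaving out two inside it.
2. **A log-rank p-value with a Cox hazard ratio is common practice.** True, and not an error in itself. What remains is that the article does not say which is primary.
3. **Omitting centre is defensible.** This stands in full. With about 60/5 = 12 patients per centre, the checks above show that entering or stratifying by centre does more harm than good.
4. **No target is missed.** Also true: the study disclaims power for efficacy.

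A reader might go further and infer that the primary comparison has a wrong error rate. The article does not support that. It gives no prognostic strengths, the log-rank size is about nominal unless the effects are strong, and the departure is then towards caution. Nor does it support the inference that the planned analysis loses substantial power, since the planned Cox model already holds ECOG, the strongest factor under the assumptions used.

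**Conclusion.** The mismatch between allocation and analysis is real, and the primary PFS comparison is not identified. The size is modest. With strong assumed effects the plain log-rank is mildly conservative (about 3.6-4.1%). Its power deficit at HR 0.5 against a Cox model with ECOG and location is about 4 points under moderate and 8 under strong effects, and slightly different test sizes account for part of it. Most of it is recovered by the ECOG term already planned, and naming location adds about 1-2 points.

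These figures rest on assumed prognostic strengths, a 2-month exponential PFS and models without prior lines or liver metastases. The mismatch itself and the missing ranking rest on the text alone. Severity is minor: the benefit is mainly a clearer and somewhat more precise effect estimate for phase III.

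**What to change.** - Name one primary PFS analysis: a Cox model with arm, ECOG (0-1 vs 2), primary tumour location (colon vs rectal), number of prior lines and liver metastases. Close the list, and take the HR, CI and p-value from this model.
- Report the plain log-rank as a sensitivity analysis, with a re-randomisation test that replays the minimisation as a check on the error rate.
- Do not enter centre as indicator terms or as a required stratum at n = 60. State why it is left out of the primary model, and examine it in a sensitivity analysis.

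The cost is wording only. Tumour location is already recorded, since minimisation needs it. The downside is one more parameter and a test size that may sit slightly above nominal (about 5-6% in the simulations), which the re-randomisation test would show.
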